### Sample size calculation

2.3

The primary outcome measure is the 12-month rate of moderate-to-severe AECOPD. Based on prior literature, the annual exacerbation frequency in patients with moderate-to-severe COPD ranges from 0.5 to 3.0 events, of which approximately 60% are classified as moderate or severe. Assuming a two-sided significance level (*α*) of 0.05 and a statistical power (1 − *β*) of 0.80, and informed by preliminary data and published evidence suggesting that PR interventions reduce exacerbation frequency by approximately 20% (risk ratio [RR] = 0.80), sample size calculations performed using PASS 2023 software indicated a requirement of 267 participants per group. Accounting for an estimated attrition rate of 10%, which is considered feasible given the chronic disease management context in the Shijiazhuang region, a 10% inflation factor was applied, yielding a final required sample size of 294 participants per group and a total sample of 588 participants.

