##### The primary outcome is the 12-month rate of moderate-to-severe AECOPD

3.1.1.1

Defined as the number of moderate or severe acute exacerbation events occurring per patient during the 12-month follow-up period. AECOPD is defined as an acute deterioration of respiratory symptoms (dyspnea, cough, and/or sputum production) requiring treatment with systemic corticosteroids and/or antibiotics, or necessitating hospitalization (10). Exacerbation data will be ascertained through review of the hospital information system and confirmed via structured telephone follow-up.

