### Statistical analysis

3.4

Data will be analyzed using SPSS version 23.0 and R (version 4.2 or above). The following analytical approaches will be employed:

(1) Data description: continuous variables will be assessed for normality using appropriate statistical tests. Normally distributed data will be expressed as mean ± standard deviation (x̄ ± s); non-normally distributed data will be presented as median (interquartile range). Categorical variables will be summarized as frequencies (*n*) and proportions (%).(2) Between-group comparisons: categorical variables will be compared using the chi-square test or Fisher’s exact test, as appropriate. Normally distributed continuous variables will be analyzed using the independent samples t-test; within-group pre-post comparisons will employ the paired t-test. Non-normally distributed variables will be analyzed using non-parametric equivalents (Mann–Whitney U test or Wilcoxon signed-rank test). Multiple group comparisons will utilize one-way analysis of variance (ANOVA) with appropriate post-hoc correction (LSD or Bonferroni). Longitudinal data across repeated time points will be analyzed using repeated measures ANOVA or generalized estimating equations (GEE).(3) Multivariable analysis: to delineate the independent association between the IoT intervention and primary outcome measures (e.g., pulmonary function improvement, AECOPD frequency, readmission rate), multivariable logistic regression or Cox proportional hazards models will be employed, with adjustment for pre-specified potential confounders (including age, sex, comorbidities, and smoking history).(4) Missing data: missing data for key variables will be addressed using single and multiple imputation techniques to preserve sample integrity and maximize analytical efficiency.(5) Significance threshold: all statistical tests will be two-sided, with a significance level of *p* < 0.05. Where applicable, multiple testing corrections (e.g., Bonferroni correction) will be implemented to control the family-wise type I error rate.

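### The primary outcome is a per-patient event count, but the only adjusted models named for it are logistic and Cox regression, which as normally used drop repeat events and do not estimate a 12-month rate ratio

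*Protocol article*

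**What the plan says.** Section 3.1.1.1 fixes the primary outcome as a count: "Defined as the number of moderate or severe acute exacerbation events occurring per patient during the 12-month follow-up period". Section 2.3 states the target effect in terms of frequency but labels it a risk ratio: "PR interventions reduce exacerbation frequency by approximately 20% (risk ratio [RR] = 0.80". It gives no single control rate. It says that "the annual exacerbation frequency in patients with moderate-to-severe COPD ranges from 0.5 to 3.0 events", "of which approximately 60% are classified as moderate or severe".

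Section 3.4, item (3), covers the association of the intervention with "primary outcome measures (e.g., pulmonary function improvement, AECOPD frequency, readmission rate" and similar measures. For these, "multivariable logistic regression or Cox proportional hazards models will be employed", with adjustment for confounders. Exacerbation frequency is thus expressly among the outcomes given to those two models.

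Item (2) of the same section lists generic methods. The entry closest to recurrent data reads "Longitudinal data across repeated time points will be analyzed using repeated measures ANOVA or generalized estimating equations (GEE". It names no count distribution, link or offset, and it is not tied to the primary outcome.

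**The concern.** Logistic regression needs a yes/no outcome, so a patient with four exacerbations counts the same as a patient with one. Cox regression in its usual form stops at the first event. Neither estimates the ratio of 12-month event rates that the outcome definition implies. Logistic regression also takes no account of time at risk. That time will differ between patients, since section 2.3 plans for 10% attrition and section 2.2.3 withdraws patients for death, loss to follow-up and other reasons.

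Repeat events should be common. Section 2.2.1 requires at least two moderate exacerbations or one severe exacerbation in the previous year. Because allocation follows preference and technology readiness (section 2.4), the adjusted model carries the inference, so the mismatch falls on the main result.

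**Working it through.** **Inputs from the article:** 267 per group before attrition, two-sided alpha 0.05, power 0.80, ratio 0.80, 0.5 to 3.0 exacerbations a year, 60% of them moderate or severe. The implied control rate for the primary outcome is 0.60 × 0.5 = 0.3 to 0.60 × 3.0 = 1.8 a year. **Assumption:** the article gives no dispersion, so k = 0, 0.5 and 1 are shown.

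**1. The plan's own figure.** The formula is not stated. Take two proportions, 0.60 and 0.60 × 0.80 = 0.48, with unpooled variance:

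n = (1.96 + 0.842)² × (0.60×0.40 + 0.48×0.52) / 0.12² = 7.849 × 0.4896 / 0.0144 = 266.9, i.e. 267.

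Then 267 × 1.10 = 293.7, i.e. 294 per group and 588 in total. This match uses only figures in the article, but it treats 60% as a proportion of patients where the text gives it as a share of events. A rate-ratio formula, n = (1.96 + 0.842)² × (1/r + 1/(0.8r) + 2k) / (ln 0.80)², reaches 267 at r = 1.33 a year with k = 0, at 2.06 with k = 0.3 and at 3.24 with k = 0.5. The first is not a figure in the article, and the other two lie above 1.8.

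**2. Power at 267 per group when the true rate ratio is 0.80.**

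- Count model: SE = √[(1/r + 1/(0.8r) + 2k)/267]; power = Φ(0.2231/SE − 1.96).
- Any-event analysis: P(any) = 1 − (1 + k·m)^(−1/k), or 1 − e^(−m) at k = 0, for mean m = r and 0.8r; then the power of a two-proportion comparison.

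Example, r = 1.2 and k = 0.5: SE = √[(0.833 + 1.042 + 1)/267] = 0.1038, and 0.2231/0.1038 − 1.96 = 0.19, so power is 58%. P(any) is 1 − 1.6⁻² = 0.609 against 1 − 1.48⁻² = 0.543, and power is 34%.

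| Control rate per year | k = 0: count vs any-event | k = 0.5 | k = 1 |
|---|---|---|---|
| 0.3 | 27% vs 24% | 24% vs 21% | 22% vs 18% |
| 0.6 | 47% vs 37% | 39% vs 29% | 33% vs 23% |
| 1.2 | 76% vs 51% | 58% vs 34% | 46% vs 25% |
| 1.8 | 90% vs 54% | 68% vs 33% | 53% vs 24% |

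**3. Events left unused.** At r = 1.2 and k = 0.5, total events are 267 × 1.8 × 1.2 = 577 and patients with any event are 267 × (0.609 + 0.543) = 308, so 47% of events are repeats. Over the whole grid this share runs from 12% (0.3 a year, k = 0) to 62% (1.8 a year, k = 1).

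**4. Cox on first events** (simulation, 600 trials per setting, complete follow-up). At k = 0.5 the mean hazard ratio is 0.81, 0.83 and 0.84 at rates 0.6, 1.2 and 1.8, with power about 32%, 37% and 42%. The count model has 39%, 58% and 68%.

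**5. The scale of the estimate.** At r = 1.2 and k = 0.5, a true rate ratio of 0.80 appears as a risk ratio of 0.543/0.609 = 0.89 and an odds ratio of 0.76. On the 60% vs 48% planning basis, logistic regression would report (0.48/0.52)/(0.60/0.40) = 0.62.

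**6. Size needed for a rate-ratio analysis with 80% power** (per group before attrition, k = 0 / 0.5 / 1): 1183 / 1340 / 1498 at 0.3 a year; 592 / 749 / 907 at 0.6; 296 / 454 / 611 at 1.2; 198 / 355 / 513 at 1.8.

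**The case against.** The strongest reply is that the planned model may agree with the sample size. Section 2.3 writes risk ratio, 267 reproduces exactly as 60% vs 48%, and on that basis logistic regression on any event has about 79% power. A reader might infer that the trial was sized on a rate ratio, and the article does not establish that. This part of the reply stands. It moves the problem rather than removing it: the model and the calculation would then both depart from the count defined in section 3.1.1.1.

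Other limits also stand:

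- Section 3.4 does not say that Cox will use first events only. Cox can be extended to recurrent events and GEE can fit counts, but neither is specified for the primary outcome. Cox also handles unequal follow-up, so that criticism applies to logistic regression alone.
- At the low end of the implied rates the power loss is small. The shift in the odds ratio depends on dispersion: at k = 1 the odds of any event equal the mean count, so the odds ratio is exactly 0.80.
- A reader might infer that the primary test will be an unadjusted rank test, from "Non-normally distributed variables will be analyzed using non-parametric equivalents (Mann–Whitney U test or Wilcoxon signed-rank test". That is a generic list, and sections 2.4 and 4 promise adjustment.
- A reader might infer that the word between logistic and Cox allows a choice after seeing the data, with inflated type I error. Item (3) covers several outcomes, so it may mean a model for each outcome type. The text does not settle this, and no inflation has been quantified.

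An unseen analysis plan does not answer the main point. The article names models for exacerbation frequency, and they do not fit its definition.

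**Conclusion.** The mismatch is real and lies in the stated text. The primary outcome is a count over 12 months, and the adjusted models assigned to it are, as normally used, for binary or first-event data. Following the article would leave the defined rate comparison unestimated.

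The cost in power ranges from about 3 percentage points at 0.3 events a year to 29 to 36 points at 1.8. The entry criteria make the higher rates more plausible. These figures rest on 267 analysable patients per group, full follow-up, a true rate ratio of 0.80 and an assumed dispersion. The direction is the same for k from 0 to 1. The count model itself falls below 80% power across most of this range, so the sample size section is also involved. This must be fixed before outcome data are seen.

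**What to change.** In section 3.4, name one primary model: negative binomial regression of the number of moderate or severe exacerbations, with log time at risk as offset, and group plus the pre-specified confounders as covariates. Report the adjusted rate ratio with its 95% confidence interval, using robust or bootstrap variance if propensity weights are applied. Keep Cox time to first event and logistic any event as supportive analyses, and state which model serves each other outcome in item (3).

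In section 2.3, say whether 0.80 is a rate ratio or a risk ratio, and restate the power for the rate-ratio analysis with a stated control rate and dispersion.

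No new data are needed, and the planned R software fits this model. The cost is more than a change of wording: the stated power is likely to be less favourable, and at 267 per group it may be well short of 80%.

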### Participant recruitment and group allocation

2.4

Eligible patients will be identified and recruited by clinicians within the Department of Respiratory and Critical Care Medicine at Shijiazhuang People’s Hospital. Research nurses will provide prospective participants with comprehensive information regarding the study. Given the inherent nature of the intervention—which necessitates active patient engagement with technology—strict randomization may compromise adherence and ecological validity. Therefore, following the provision of written informed consent, participants will be allocated to either the IoT-assisted PR group or the conventional PR group based on their initial preference and a preliminary assessment of technology readiness and digital competency (e.g., smartphone ownership, basic digital literacy). This pragmatic allocation approach is designed to reflect real-world implementation conditions. Participants who initially prefer conventional care but express willingness to engage with IoT technology will be encouraged to join the IoT-assisted PR group to maximize recruitment efficiency. Baseline characteristics of both groups will be rigorously compared and statistically adjusted in all subsequent analyses. We acknowledge that an attention-matched control group is not feasible in this pragmatic study design due to resource constraints and the inherent nature of the IoT intervention. This limitation will be discussed more clearly in the Discussion section.

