### Covariates

3.2

Baseline data will be systematically collected, encompassing: demographic characteristics (age, sex, educational attainment, living arrangements, and health insurance type); disease characteristics (COPD duration, GOLD grade, prior exacerbation history, and comorbidity burden quantified using the Charlson Comorbidity Index); smoking history; current pharmacological regimen; and baseline pulmonary function parameters. We acknowledge that allocation based on patient preference and technology readiness may introduce selection bias. Patients who are more comfortable with smartphones and IoT devices may also be younger, more educated, more motivated, more adherent, or have better social support. All of these factors could influence the outcomes. Therefore, the following additional variables will be collected to allow for statistical adjustment: digital literacy, baseline motivation, and socioeconomic status.

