Several potential challenges and corresponding mitigation strategies have been considered when performing the study. First, to address device usability issues and the digital divide among elderly patients, one-on-one training will be provided at enrollment, supplemented by illustrated user manuals, a dedicated technical support helpline, and reserve equipment. Second, data privacy and security concerns will be managed through comprehensive informed consent, enterprise-grade encryption and de-identification protocols, compliance with applicable cybersecurity legislation, and regular security audits. Third, to sustain long-term adherence, a multidimensional approach will be implemented, including personalized rehabilitation progress reports, peer support networks, regular proactive telephone follow-up, and timely outreach to participants with no data upload for three consecutive days. Fourth, to mitigate potential confounding bias inherent in the non-randomized design, a comprehensive set of covariates—including disease severity, comorbidity burden, and socioeconomic status—will be collected and adjusted for using multivariable regression and propensity score analyses, with sensitivity analyses conducted to evaluate the robustness of the primary outcome findings. Finally, we acknowledge that an attention-matched control group is not feasible in this pragmatic study design due to resource constraints and the inherent nature of the IoT intervention. Digital literacy, access to technology, acceptability, and user-centric design may significantly influence both group assignment and outcomes. As highlighted by Mishra et al. in their systematic review on digital interventions for COPD (25), factors such as usability, user-centric design, technology acceptance and adoption play critical roles in the effectiveness of digital interventions. Patients with higher digital literacy and better access to technology may be more likely to be assigned to or accept the IoT intervention, and may also achieve better outcomes regardless of the intervention itself. These factors will be measured at baseline and adjusted for in the primary analyses.

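### Section 3.4 does not carry through the confounding control that Sections 2.4, 3.2 and the Discussion promise for a preference-allocated comparison

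*Protocol article*

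**What the plan says.** **Allocation (Section 2.4).** Arms are assigned "based on their initial preference and a preliminary assessment of technology readiness and digital competency (e.g., smartphone ownership, basic digital literacy". There is no randomisation.

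**What is promised.**
- Section 2.4: "Baseline characteristics of both groups will be rigorously compared and statistically adjusted in all subsequent analyses".
- Section 3.2: "the following additional variables will be collected to allow for statistical adjustment: digital literacy, baseline motivation, and socioeconomic status". The same section lists prior exacerbation history, GOLD grade and baseline lung function among the baseline data.
- Discussion: disease severity, comorbidity burden and socioeconomic status "will be collected and adjusted for using multivariable regression and propensity score analyses". On digital literacy, access to technology and acceptability it says: "These factors will be measured at baseline and adjusted for in the primary analyses".

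**What Section 3.4 specifies.**
- Item (2), on between-group comparisons: "Normally distributed continuous variables will be analyzed using the independent samples t-test; within-group pre-post comparisons will employ the paired t-test", with rank-based and chi-square equivalents. For repeated measurements: "Longitudinal data across repeated time points will be analyzed using repeated measures ANOVA or generalized estimating equations (GEE". No covariates are named.
- Item (3): logistic or Cox models "with adjustment for pre-specified potential confounders (including age, sex, comorbidities, and smoking history".
- Item (4): single and multiple imputation.
- Propensity scores are not mentioned in any item.

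**The concern.** In a study where patients sort themselves by preference and readiness, an unadjusted difference between arms mixes the intervention effect with the difference between the kinds of patient who choose each arm. The protocol expects this. Section 3.2 says that technology-comfortable patients may differ in age, education, motivation, adherence and social support, and that these could influence outcomes. The Discussion adds that such patients may do better whatever the intervention does. By the authors' own account, the likely bias favours the IoT arm.

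Adjustment is therefore the main protection for the conclusion, and the section that says how the data will be analysed should contain it. As written, an analyst who follows item (2) breaks the promise in Section 2.4. An analyst who adjusts only for the covariates named in item (3) does not deliver the Discussion's promise. Three different results (unadjusted, adjusted for four covariates, propensity-adjusted) could each be defended from the text after the data are seen.

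Prior exacerbation history deserves separate mention. It is the baseline counterpart of the primary outcome, so leaving it out gives up both bias control and precision.

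**Working it through.** **1. Passages side by side.**

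| Item | Promised | Named in 3.4 |
|---|---|---|
| Adjustment in all analyses | 2.4 | No: two-sample tests in item (2) cannot adjust |
| Age, sex, comorbidities, smoking | 2.4 (general) | Yes, item (3) |
| Digital literacy | 3.2, Discussion | No |
| Access to technology | Discussion | No |
| Baseline motivation | 3.2 | No |
| Socioeconomic status | 3.2, Discussion | No |
| Prior exacerbation history | Listed in 3.2; covered by 2.4 only in general terms | No |
| Propensity score analysis | Discussion | No |

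The finding rests on this table. The arithmetic below only shows what could be at stake.

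**2. The plan's own figures (Section 2.3).** The 267 per group is reproduced by two proportions, 0.60 versus 0.60 × 0.80 = 0.48, two-sided 0.05, power 0.80, unpooled: 7.849 × (0.24 + 0.2496) / 0.12² = 266.9. Reading 60% as a per-patient proportion is my assumption. Then 267 × 1.10 = 293.7, giving 294. The calculation has no term for covariate adjustment, so it neither supports nor weakens this point. From it I take only the effect (0.80) and the power. Together they imply a standard error on the log scale of |ln 0.80| / (1.96 + 0.84) = 0.2231 / 2.80 = 0.0797.

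**3. Illustrative bias (assumed inputs).** Take a binary trait with rate ratio g and prevalences p₁ (IoT) and p₀ (control), left out of the model, with no true intervention effect:

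false rate ratio b = [1 + (g − 1)p₁] / [1 + (g − 1)p₀]

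- g = 0.75, 70% vs 30%: 0.825 / 0.925 = 0.892
- g = 0.75, 80% vs 20%: 0.80 / 0.95 = 0.842
- Mild harmful trait, g = 1.2, 40% vs 50%: 1.08 / 1.10 = 0.982
- Strong harmful trait, g = 2.0, 30% vs 70%: 1.30 / 1.70 = 0.765

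With δ = |ln b| / 0.0797, the false-positive rate is Φ(−1.96 + δ) + Φ(−1.96 − δ):

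- b = 0.892: δ = 1.44, rate about 0.30
- b = 0.842: δ = 2.16, rate about 0.58
- Across the range 0.982 to 0.765: about 0.06 to 0.92, against a nominal 0.05

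**4. Illustrative cost of strong adjustment.** Suppose the same trait drives allocation, arms are equal in size, and overlap weights are used. The effective fraction of each arm is (mean weight)² / mean squared weight.

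- 80% vs 20%: mean weight 0.8 × 0.2 + 0.2 × 0.8 = 0.32; mean square 0.8 × 0.04 + 0.2 × 0.64 = 0.16; fraction 0.32² / 0.16 = 0.64. The standard error rises by 1/√0.64 = 1.25, and power falls from 80% to Φ(2.80/1.25 − 1.96), about 61%.
- 70% vs 30%: mean weight 0.42, mean square 0.21, fraction 0.84, power about 73%.

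**The case against.** The strongest reply is that the sections add to one another and do not conflict. The list in item (3) is introduced as inclusive, so it does not shut out the variables in Section 3.2. The authors acknowledge the selection problem, collect the variables and commit to adjusting for them. A journal article may leave the full covariate set and the propensity specification to an analysis plan. Much of this stands, and it limits what can be claimed. A reader might infer the following, none of which the documents support:

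- *That the readiness variables are excluded.* They are not named in 3.4; nothing excludes them.
- *That the named covariates are unrelated to allocation.* Section 3.2 itself links age to comfort with technology.
- *That adjustment for prior exacerbations was explicitly promised and then dropped.* It is covered only by the general sentence in 2.4 and, arguably, by disease severity in the Discussion. Eligibility also restricts everyone to patients with a recent exacerbation history, which narrows any imbalance without removing it.
- *That all secondary outcomes get unadjusted tests, and that patients who miss a visit are lost.* Item (2) assigns no test to 6MWD, CAT or SGRQ by name. GEE is offered and can carry covariates, item (3) puts pulmonary function in the adjusted models, and item (4) plans imputation.
- *That paired tests are offered as evidence of a group effect.* The text does not say so.
- *That 0.89 or 0.84 measures the bias in this study.* The inputs are assumed, and they describe a trait left wholly unadjusted and uncorrelated with the adjusted covariates.

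The reply does not dispose of item (2). That item does more than stay silent: it prescribes tests that cannot adjust for between-group comparisons, against a promise to adjust in all analyses. Some of those tests may be meant only for comparing baseline characteristics, but the text does not say so.

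**Conclusion.** The point holds as a failure to carry commitments from Sections 2.4, 3.2 and the Discussion into Section 3.4. It has two parts. Item (2) specifies unadjusted two-sample tests, and longitudinal methods with no covariates named, in conflict with Section 2.4. Item (3) does not name the readiness, motivation, socioeconomic or exacerbation-history variables, and 3.4 does not mention the promised propensity analysis.

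This rests on the text and needs no assumption. The size of the resulting bias cannot be identified from the documents. The illustrations show only that, under the assumed inputs, one omitted trait could produce a false rate ratio anywhere from close to 1 to beyond the planned 0.80. It should be settled before outcomes are compared by arm, because the present wording leaves the choice of reported estimate open.

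**What to change.** In Section 3.4:

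- State that all treatment-effect estimates, primary and secondary, come from models adjusted for one pre-specified covariate set. To the four covariates named, add prior-year exacerbation history, baseline severity (GOLD grade or FEV₁), digital literacy, technology access, baseline motivation and socioeconomic status.
- For longitudinal secondary outcomes, use GEE, which is already offered, or a mixed model. Adjust for the baseline value of the outcome and the same covariate set, in place of two-sample tests and repeated-measures ANOVA.
- Bring in the propensity score analysis promised in the Discussion, with a check of overlap between arms. The choice of weighting or matching can stay with the sponsor.
- Limit unadjusted two-sample tests and within-group paired tests to description.

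The cost is wording and modest programming, because the data are already planned. One detail needs care: technology access is assessed at allocation (2.4) and promised as a baseline measure in the Discussion, but it is not in the Section 3.2 list and should be added there. The real downside is precision. If readiness nearly determines the arm, the loss could be material, as in the fall to about 61% power in the 80% versus 20% illustration, which is why the overlap check belongs in the plan.
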